### Control condition

The control group will receive care as usual, during the trial and follow-up period. NHs in the control group have to show a satisfactory standard of care. This standard will be verified by the COSMOS team during the data collection. In addition, the control group will be monitored by monthly telephone contact. The control group may also derive a considerable learning effect. Before randomization, representatives from each NH receive information about the aim and content of COSMOS, because they have to decide whether they are interested in participating or not. When NHs are then randomized for control, responsible staff members receive information on dementia diagnoses, neuropsychiatric symptoms and pain assessment in people with dementia as part of the data collection, and they will be trained in the use of primary/secondary outcome measures. To motivate control NHs to continue participating, they will receive the COSMOS intervention after the last data collection at month 9 by a waiting-list-strategy [47] supported by a “supervisor” recruited from a NH who has already received the intervention.

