#### Cluster design and blinding

According to the research design, patients, units or even NHs are cluster randomized to care as usual or treatment. In a hybrid trial design, the implementation strategies, education and follow-up may be optimized during the process, for the purpose of gaining new understanding and insight. Because of this, the participants, patients and/or staff related to the clusters cannot be completely blinded regarding the group allocation. Meanwhile, the cluster randomized design is the most suitable design for implementation research, as it reduces the contamination between the intervention and control groups [46]. Furthermore, the cluster design takes into account the fact that the participants live together in the NH clusters.

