### Effectiveness measures by core outcome measurements

Data collection for outcome measures will be completed at baseline, months 4 and 9, conducted by the patient’s primary caregiver who knows the patient, together with a research assistant. Demographics will be collected from the patients’ record. Selection of outcome measures is consistent with recommendations from the Initiative on Methods, Measurement and Pain Assessment in Clinical Trials (IMMPACT) [48].

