## Trial status

The trial is an ongoing project; we have completed the pilot, included participants in the trial and now commenced implementation of the COSMOS intervention and data collection at baseline and follow-up, at the time of manuscript submission.

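### Outcome-scale training is placed after randomization, at least in control homes, so baseline ratings appear to be made with the arm known

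*Protocol article*

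**What the plan says.** The Control condition section sets out an order of events. First, "Before randomization, representatives from each NH receive information about the aim and content of COSMOS", so that the homes can decide whether to take part. Randomization follows. Then: "When NHs are then randomized for control, responsible staff members receive information on dementia diagnoses, neuropsychiatric symptoms and pain assessment". This information is given "as part of the data collection, and they will be trained in the use of primary/secondary outcome measures". The sentence concerns control homes; no matching sentence dates scale training in intervention homes.

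On who rates and when, the section on effectiveness measures says: "Data collection for outcome measures will be completed at baseline, months 4 and 9, conducted by the patient’s primary caregiver who knows the patient". A research assistant takes part, and the article does not say whether the assistant is blinded. Cluster design and blinding says that "the participants, patients and/or staff related to the clusters cannot be completely blinded regarding the group allocation".

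The primary outcome is quality of life by QUALID and QUALIDEM, and Table 1 marks both as proxy rated. Data management and analyses plans ANCOVA and a repeated-measures mixed model of change over time. No section says whether consent or baseline rating came before or after a unit's allocation was disclosed. The flow chart (Fig. 2) is not shown.

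**The concern.** Open delivery cannot be avoided in this design, but baseline rating with the arm known can be. A baseline score is useful for adjustment because allocation cannot have influenced it. A caregiver who knows the arm may score differently at the start: intervention staff expect improvement, and control staff know they are on a waiting list. If the arms differ at baseline for that reason, an analysis that uses the baseline turns part or all of the difference into an apparent treatment effect. Covariate adjustment does not remove it, because the covariate itself is affected. The primary outcome is exposed, since both of its instruments are scored by proxy.

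**Working it through.** **Order of events.** The conclusion rests on four steps.

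1. Control homes are randomized, and their responsible staff are then trained in the outcome scales (Control condition). This is stated.
2. The training is tied to data collection (same sentence). This is stated.
3. The primary caregiver, with a research assistant, applies the scales at baseline, month 4 and month 9 (Effectiveness measures). This is stated.
4. Raters are trained on a scale before first using it. This is inferred; the article does not say it.

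From 1 to 4, baseline in control homes follows randomization. With staff not completely blinded, it appears to be rated with the arm known. No visible sentence contradicts this, and none confirms it with a date.

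For intervention homes there is only a partial pointer. The appendix (Table 2) puts practical exercises with the MOBID-2 Pain Scale, a secondary outcome, into the 2-day education, which the abstract assigns to the intervention group. Training on that scale therefore depends on allocation there too, but the article does not say whether it precedes baseline.

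**Size.** The plan has no figure of its own on this point to reproduce. The following is an illustration.

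Inputs:
- Planned standardized effect size 0.4; ICC 0.157; upper drop-out rate 25% (Sample size analyses).
- 571 patients in 67 units (Methods and design).
- Assumed, not in the document: an arm-related shift b in baseline ratings of 0.05, 0.10 or 0.20 SD, with none at month 4; a correlation r between baseline and follow-up of 0.5 to 0.7.

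Formulas: the bias in a change score is b; the bias in ANCOVA is about r × b. Each is divided by 0.4.

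| b (SD) | Change score: share of 0.4 | ANCOVA bias, r = 0.5 to 0.7 (SD) | ANCOVA: share of 0.4 |
|---|---|---|---|
| 0.05 | 12.5% | 0.025 to 0.035 | 6.25% to 8.75% |
| 0.10 | 25% | 0.05 to 0.07 | 12.5% to 17.5% |
| 0.20 | 50% | 0.10 to 0.14 | 25% to 35% |

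**Effect on the false-positive rate.**
- Patients at month 4: 571 × 0.75 = 428.25, or about 214 per arm and 428.25 / 67 = 6.39 per unit.
- Design effect: 1 + (6.39 − 1) × 0.157 = 1.85.
- Standard error of the month 4 difference in SD units: √(2 × 1.85 / 214) = 0.131.
- For a change score, the standard error is multiplied by √(2(1 − r)), which is 1 at r = 0.5. For ANCOVA it is multiplied by √(1 − r²), giving 0.114 at r = 0.5 and 0.094 at r = 0.7. The same design effect is assumed throughout.
- Rate = Φ(−1.96 + bias/SE) + Φ(−1.96 − bias/SE).
- Change score at r = 0.5: about 7%, 12% and 33% for b = 0.05, 0.10 and 0.20.
- ANCOVA at b = 0.10: about 7% at r = 0.5 and 12% at r = 0.7.
- With the article's own planning figure of 81 effective patients per arm, the standard error is √(2/81) = 0.157, and the change-score rate at b = 0.10 is about 10%.

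**The case against.** The strongest reply is that the article gives no trial timeline. The sentence on scale training stands in a paragraph about what control homes receive and may learn, and it covers that arm only. Nothing dates baseline against randomization. The flow chart, where the order would normally appear, is not shown, and exact scheduling is commonly left to the full protocol. This stands as a limit on certainty: the conclusion is an inference and is firmest for control homes. It does not dispose of the point, because the article is not merely silent. It states an order, and that order invites bias.

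Two stronger readings are not supported.
- A reader might infer that patients were consented after their unit's allocation was known. No sentence says so. Trial status reports participants as already included, and Ethical approval puts consent in the past tense. Neither dates consent against randomization.
- A reader might take the Trial status remark that the team has "now commenced implementation of the COSMOS intervention and data collection at baseline and follow-up" as proof that baseline ran alongside delivery. It is a status line for the whole trial and shows no order within a unit. Implementation in NHs places delivery between the baseline and month 4 data collections.

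The research assistant may offer some protection, but blinding is not stated, so this can be neither credited nor dismissed. The size of the shift is assumed and its direction unknown. A rating bias that is the same at baseline and at month 4 would cancel in a change score. The incomplete blinding of staff is already disclosed, and it affects month 4 whatever is done about baseline.

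**Conclusion.** The point holds in limited form. The article places training in the outcome scales after randomization in control homes, and baseline ratings of proxy-scored primary outcomes therefore appear to be made with the arm known. It does not establish this for intervention homes, and it does not show late inclusion of patients. Under the assumed shifts, the bias would be 12.5% to 50% of the planned effect size for change scores and about 6% to 35% for ANCOVA. The actual shift cannot be derived from the document. The conclusion rests on training preceding first use of the scales, on caregivers knowing their arm once it is allocated, and on the unseen flow chart not showing a different order. The change should be made because it is cheap and the primary outcome is affected. Confidence is medium.

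**What to change.** 1. Change the order in Control condition. In every unit not yet started, in both arms, complete rater training, baseline ratings and any remaining consent before allocation is disclosed.
2. For units already started, record per unit or patient the dates of consent, baseline rating and disclosure.
3. In the statistical analysis plan still to be developed, pre-specify a sensitivity analysis that compares month 4 scores without the baseline rating. State that it does not remove bias from month 4 ratings that are themselves unblinded.
4. If baseline did precede disclosure, correct the section to say so. That closes the point on baseline ratings.

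The cost is a reordering of existing steps and three dates in the database. Homes would learn their arm slightly later, which may delay booking of the education days. Because units are matched and randomized within municipality, units randomized together may have to wait for the slowest one. The sensitivity analysis also gives up the precision that baseline adjustment provides.

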**Fig. 3 Fig3:**
[figure not shown]
Detailed overview of the multicomponent COSMOS intervention, education program and outcome measures

**Fig. 4 Fig4:**
[figure not shown]
COSMOS protocol development and implementation strategy

### Education of the COSMOS ambassadors

The intervention will be delivered by implementers called “COSMOS ambassadors”. The COSMOS ambassadors are staff from the intervention NHs. We invite all physicians, nurses and licensed practical nurses to the education, but require a minimum of two nurses from each NH unit in the intervention group to participate. The COSMOS ambassadors usually registered and licensed practical nurses have hands-on experience with NH patients in their daily work. Ambassadors participate in the 2-day education (about 2.5 h per COSMOS component, role play, patient-centered discussion and feedback) following the COSMOS program (Fig. 3 and Appendix) and receive supervision from the research team using the COSMOS patient logs and written COSMOS guidelines. NH managers provide a written agreement for participation and confirm that staff will not switch between care units. Given the complexity and multi-faced nature of the intervention, as well as the heterogeneous “real-world” population, some variability in the implementation of the interventions is to be expected.

### Effectiveness measures by core outcome measurements

Data collection for outcome measures will be completed at baseline, months 4 and 9, conducted by the patient’s primary caregiver who knows the patient, together with a research assistant. Demographics will be collected from the patients’ record. Selection of outcome measures is consistent with recommendations from the Initiative on Methods, Measurement and Pain Assessment in Clinical Trials (IMMPACT) [48].

### Primary and secondary outcome measures

The primary outcome in the COSMOS trial is QoL as measured by quality of life in late-stage dementia (QUALID) [49] and Quality of life in Dementia (QUALIDEM) [50] (Table 1). We also use the European Quality of Life-5 Dimensions (EQ-5D) [51] in connection with Resource Utilization in Dementia-Formal Care (RUD-FOCA) [44] as one of the secondary outcomes. Other secondary outcomes are Neuropsychiatric Inventory-Nursing Home version (NPI-NH) [52], Cohen-Mansfield Agitation Inventory (CMAI) [53], Cornell Scale for Depression in Dementia (CSDD) [54], Mobilization-Observation-Behaviour-Intensity-Dementia 2 (MOBID-2) Pain Scale [55, 56], Personal Activities of Daily Living (P-ADL) [57] and Clinical Global Impression of change (CGIC) [58, 59]. We will use Actigraphy (Philips Actiwatch Spectrum) to objectively assess sleep patterns and circadian rhythm and light exposure [60, 61]. Total medication and use of psychotropic drugs in number and dose will be assessed with respect to drug-related problems and drug–drug interactions using STOPP and START criteria [43] and anticholinergic list [43]. A full description of the primary and secondary outcomes and screening instruments MMSE [41] and FAST [42] are provided in Table 1.

**Table 1 Tab1:** Instruments used as primary and secondary outcome measures

	What does the tool measure	Tool characteristics & psychometric properties
QUALID*† [49]	QoL by cognitive function, health, function, social and psychological well-being.	11 behaviours rated on a 5-point Likert scale (range 11–55). Excellent reliability, internal consistency and validity are reported. Lower score indicates higher QoL
QUALIDEM*† [50]	QoL by self-image, affect, restlessness, care and social relation, feeling at home & active.	40 items scored 0–3 in 10 subscales yielding a sum score for each subscale; care relationship (0–21), positive affect (0–18), negative affect (0–9), restless tense behaviour (0–9), positive self-image (0–9), social relations (0–18), feeling at home (0–12), having something to do (0–6), undefined items (0–9). Sufficient reliability and validity are reported
EQ-5D*† [51, 69]	QoL by mobility, self-care, activities, pain/discomfort and anxiety/depression, and impression of health	Patient or care-giver indicates patient`s state in f the 5 dimensions, according to 3 levels: no, some or extreme problems, and total impression of health (0–100). Scarce evidence for use in NH setting & with/in people with dementia
NPI-NH*† [52, 70]	Neuropsychiatric symptoms in dementia, caregiver distress.	Total and subscale scores are provided based on frequency & severity of symptoms (range 0–144). Good validity and reliability of the Norwegian version of the NPI-NH. Including The neuropsychiatric inventory caregiver distress scale
CMAI*† [53, X7]	Agitation & behavioural disturbances	29 items (range 29–203). Good validity & reliability
CSDD*† [54]	Depression in people with dementia	19 items rated from 0=no symptom to 2=severe. ≥8 = depression, >12=moderate-severe depression. Satisfactory inter-rater reliability and validity
MOBID-2 Pain Scale*† [55]	Two-part pain location and intensity in people with advanced dementia.	Pain intensity inferred by the patient’s pain behaviours during standardized, guided movements (Part 1), and pain behaviours related to internal organs, head and skin (Part 2). Excellent reliability, validity and good responsiveness
MMSE † [71]	Differentiation of severity of cognitive impairment	30-point scale where 0 to 11=severe impairment, 12 to 17=moderate, 18 to 23=mild, 24 to 30=no impairment
FAST*† [42, X14]	Severity of dementia	Stages dementia in 7 stages, 1 normal, 2 normal ageing, 3 possible dementia, 4 mild, 5 moderate, 6 and 7 severe dementia. Good reliability and validity
ADL*† [57]	Physical function by rating activities; feeding, moving, toilet and dressing.	The scale includes 6 items (range 0–30) Lower values indicates better functioning and independence
CGIC* [72]	Perceived improvement and efficacy	7-point rating ranging from very much worse (0) to very much improved (6). Not intended as a sensitive measure of small changes, but for changes considered clinically significant.
RUD-FOCA* [44]	Cost-analysis of time use during 24 hours	Total time per 24 hours is summed and mean time is calculated by records of required care. Validated for use in NHs, acceptable test-retest reliability and construct validity

* Proxy rated instrument, † Validated for use in people with dementia, *ADL* Physical Self-Maintenance Scale, *FAST* Functional Assessment Staging, *CGIC* Clinical Global Impression of Change, *CMAI* Cohen-Mansfield Agitation Inventory, *CSDD* Cornell Scale for Depression in Dementia, *EQ-5D* European Quality of Life-5 Dimensions, *MMSE* Mini Mental State Examination, *MOBID 2* Mobilization-Observation-Behaviour-Intensity-Dementia 2 Pain Scale, *NPI-NH* Neuropsychiatric Inventory- NH version, *QoL* Quality of life, *QUALID* quality of life in late-stage dementia, *QUALIDEM* Quality of life in Dementia, *RUD-FOCA* Resource Utilization in Dementia – Formal Care

### Indicators of effective implementation strategies (qualitative)

The interventions will be observed and evaluated according to i) perception among end users and stakeholders that the intervention is “agreeable” (Acceptability); ii) staff intentions and actions to employ the intervention (Adoption); iii) perceived relevance of the intervention in NH settings (Appropriateness); iv) degree to which the intervention can be carried out in NHs (Feasibility); v) integrity to and quality of intended program delivery (Fidelity); vi) extent of institutionalization of the interventions, reach or spread (Penetration); vii) maintenance and continuation of the interventions; durability; integration; incorporation (Sustainability) [62, 63]. The evaluations include analyses of medical records and interviews of staff. Assessment of the implementation of the COSMOS interventions will be completed with monthly visits and phone calls to the contact persons on each NH. The patient logs will help structure the phone conversations according to individual intervention and patient. These semi-structured interviews will be coded in accordance with the patient log. This entails registering whether or not the planned interventions have been carried out (yes/no/not applicable), and collecting short statements regarding barriers and other relevant comments.

### Data management and analyses

A data manager will be responsible for punching, validating and merging trial data. Data will be stored on approved servers at the University of Bergen (UoB). Demographic and clinical characteristics between intervention and control at baseline will be compared using Pearson *χ*^2^ test statistics for categorical variables and independent samples *t* test for normal variables (age, diagnoses and pain diagnoses). Analysis of covariance (ANCOVA) estimates the mean effect in each trial arm, weighted across clusters (1 cluster = 1 NH unit) according to number of patients within each cluster, and from this, the mean treatment effect is estimated at each time point [47]. The intraclass correlation coefficient (ICC) expresses the proportion of the total variance in data between included clusters. Primary efficacy population includes all patients with at least one post-baseline assessment (month 4 measure), and we will use a linear intercept mixed model in a two-way repeated measures configuration to assess change over time. Treatment effect will be expressed as estimated effect of intervention, along with a 95 % confidence interval and *p* values ≤0.05 for each time point. The Mann-Whitney *U* test will be used for non-normal distributed continuous variables such as QUALID [49], QUALIDEM [50], NPI-NH [52], CMAI [53], CSDD [54], MMSE [41], MOBID-2 Pain Scale [55], CGIC [59] and P-ADL [57]. Cost-utility analysis will be performed including costs for pharmaceuticals, resource use in NHs and use of external heath care facilities [44]. A full statistical analysis plan, including potential missing data imputation for each outcome measure, will be developed through the course of the study.

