**Methods/Design:**

COSMOS includes a 2-month pilot study with 128 participants distributed among nine Norwegian nursing homes, and a 4-month multicenter, cluster randomized effectiveness-implementation clinical hybrid trial with follow-up at month 9, including 571 patients from 67 nursing home units (one unit defined as one cluster). Clusters are randomized to COSMOS intervention or current best practice (control group). The intervention group will receive a 2-day education program including written guidelines, repeated theoretical and practical training (credited education of caregivers, physicians and nursing home managers), case discussions and role play. The 1-day midway evaluation, information and interviews of nursing staff and a telephone hotline all support the implementation process. Outcome measures include quality of life in late-stage dementia, neuropsychiatric symptoms, activities of daily living, pain, depression, sleep, medication, cost-utility analysis, hospital admission and mortality.

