### Sample size analyses

QoL is our primary outcome measure, and ongoing comparable intervention studies conduct similar sample size analyses; however, we are not aware of large-scale studies presenting the effect of a multicomponent intervention on QoL outcome measures such as QUALIDEM or DEMQOL. Based upon the magnitude of improvement in our previous RCT on pharmacological interventions [15] for neuropsychiatric symptoms in NH patients, we estimated that a 25 % reduction of the NPI-NH scale (SD 5 standardized effect size [SES] 0.4) for comparison of the intervention and control group at month 4. To measure a difference of this magnitude requires a minimum of 81 patients allocated to each arm of the trial, for a significance level of 5 % (two sided), a power of 80 % and equal allocation. As cluster designs lead to loss of power [47], the sample size should be multiplied by 1 + (*m* − 1)*ρ*, called the design effect, where *m* is the average cluster size and *ρ* = s2b/(s2b + s2w) is the ICC, where s2b is the variance between clusters, and s2w is the variance within clusters. Based on additional assumption of an estimated ICC of 0.157 in the earlier trial with an intervention over 8 weeks [15], an average of 10 eligible patients in each cluster gives a DE = [(1 + (11 − 1) × 0.157)] = 2.57 [15]. Thus, we need a minimum of 208 (2.57 × 81) patients per arm, or 416 patients in total. We expect a drop-out rate between 20 to 25 % [64] from baseline to month 4. Thus, we need a recruitment of an additional 104 participants (520 in total), with 32 clusters (NH units) in each arm. COSMOS will be conducted in at least 64 NH units (clusters), with an average of 8–12 patients on each unit.

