## Discussion

COSMOS intends to improve the QoL in NH patients by enhanced communication and ACP, systematic assessment and treatment of pain, medication review and organization of meaningful activities provided by educated NH staff. Thereby, the intervention aims to improve the mental and physical health of the people, safety and cost-effectiveness and reduce unnecessary medication and hospital admission.

The development of the multicomponent approach is built on evidence-based research results of single-intervention studies. In fact, this intervention was inspired by prompt feedback from NH staff in response to our pain research: “of course, it is important that NH patients are pain free, but our problem is not primarily the pain, but rather the communication—we do not talk to them, early enough” or “nice with less medication, but our problem is lack of activities”. Our research team realized that complex health challenges in NHs are in need of complex and multifaceted and systematic interventions.

In the absence of a comparable study design, the length of a 4-month period is based on current results by a trajectory study demonstrating a death rate of 29 % during the first year after NH admission (submitted). Based on the 2-month pilot study, we recognized that the NH staff needs enough time to get familiar with the COSMOS intervention, teach new colleagues and make necessary changes in the unit. On the other hand, the study period should not be too long, to avoid patient drop-out and ensure staff compliance.

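### The primary efficacy population requires a post-baseline (month 4) assessment, an exclusion after randomisation that leaves out about 20-25% of patients on the plan's own figures

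*Protocol article*

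**What the plan says.** All references are to the Protocol article.

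- **Data management and analyses** defines the set: "Primary efficacy population includes all patients with at least one post-baseline assessment (month 4 measure". The same sentence chooses a repeated-measures linear mixed model. The section also plans an ANCOVA without naming its covariates. It defers possible imputation to a later analysis plan, but it fixes the population here.
- **Effectiveness measures by core outcome measurements** schedules assessments at baseline, month 4 and month 9.
- **Sample size analyses** gives the expected loss: "We expect a drop-out rate between 20 to 25 % [64] from baseline to month 4".
- **Discussion** justifies the short study period by a trajectory study "demonstrating a death rate of 29" per cent in the first year after admission.
- **Abstract, Methods/Design** lists the outcomes as "quality of life in late-stage dementia, neuropsychiatric symptoms, activities of daily living, pain, depression, sleep, medication, cost-utility analysis, hospital admission and mortality", so death and hospital admission are themselves outcomes.

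No intention-to-treat or all-randomised population is named.

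**The concern.** A patient enters the primary population only by being alive, present and assessed four months after the unit was allocated. The groups compared are then no longer the groups randomised.

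The article gives reasons why loss could differ by arm:

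- Patients and staff cannot be fully blinded.
- Control homes are promised the intervention after month 9 expressly to keep them taking part.
- The intervention includes advance care planning and medication review, and is hypothesised to reduce hospital admissions, so it may change who can still be assessed.

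If loss differs by arm and the lost patients differ from those retained, part of the observed difference in quality of life reflects who remains. The restriction is also unnecessary, because the chosen model does not need complete follow-up.

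**Working it through.** **1. The plan's own figures.** 81 × 2.57 = 208.2 per arm, or 416 in total. Allowing for 20% loss, 416 / (1 − 0.20) = 520, which matches "Thus, we need a recruitment of an additional 104 participants (520 in total), with 32 clusters (NH units) in each arm". At 25% the target would be 416 / 0.75 = 555; the 571 included exceed this.

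**2. Patients outside the primary population.** Number = N × expected loss to month 4.

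| N | 20% lost | 25% lost | Retained |
|---|---|---|---|
| 520 (target) | 104 | 130 | 416-390 |
| 571 (included) | 114 | 143 | 457-428 |

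**3. Deaths within that loss.** The article does not split drop-out by cause. If the 29% first-year rate applied here at a constant hazard, 1 − 0.71^(4/12) = 10.8% would die by month 4, about 62 of 571. This is an assumption. The rate is for the first year after admission, and the trial excludes patients with a life expectancy of 6 months or less, which may lower it.

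**4. Bias from unequal loss.** The mean of retained patients equals the overall mean minus p × g, where p is the proportion lost and g is the mean of the lost minus the mean of the retained. If g is the same in both arms, an unadjusted comparison of completers is biased by (p₀ − p₁) × g. If p₁ = p₀, the bias is zero.

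**5. What the choice of population changes.** A simulation assumed standardised scores, a baseline to month 4 correlation of 0.6, no true effect, and 17.5% v 27.5% lost. Bias in SD:

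| Analysis | Loss driven by baseline | Loss driven by month 4 outcome |
|---|---|---|
| Unadjusted month 4 difference, completers | 0.041 | 0.067 |
| Change from baseline, completers | 0.026-0.027 | not tabulated |
| Baseline-adjusted ANCOVA, completers | 0.000 | 0.044 |
| Repeated-measures model, all patients | about 0 | about 0.04 |

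With equal loss of 20% in both arms, the bias was zero.

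Hand check of the baseline column: a month 4 shift of 0.041 at correlation 0.6 implies a baseline shift among completers of 0.041 / 0.6 = 0.068. The change score then moves by (1 − 0.6) × 0.068 = 0.027 in size. By step 4, 0.068 / 0.10 means that lost patients were about 0.68 SD worse at baseline than retained ones.

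**The case against.** Several points on the other side stand.

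- **The wording is ambiguous.** With two follow-up visits, requiring at least one assessment could admit a patient seen only at month 9; the parenthesis points the other way. A reader might infer that such patients are certainly excluded, but the text does not settle it. Patients never assessed after baseline are excluded on either reading.
- **Adjustment may already do the work.** If loss is predicted by baseline, a baseline-adjusted analysis of completers is unbiased, and baseline-only patients add almost nothing to the arm contrast. The gain arises if the model contrasts change without such adjustment, which the article leaves open, and from using month 9-only patients.
- **Including everyone is not a cure.** If loss depends on the unseen outcome, about 0.04 SD of bias remains. A missing-at-random model also implies quality-of-life values after death, which are undefined.
- **Details belong to the analysis plan.** Imputation and sensitivity analyses are commonly settled there, and their absence is no fault. But imputation within a set that already requires a follow-up measure cannot restore those outside it.

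Two stronger readings should be resisted. A reader might add early deaths to the 20-25%; the article does not separate them, and they probably lie inside it. A reader might also multiply a 5-10 point difference in loss by a gap of 0.5-1.0 SD, giving 0.025-0.10 SD, and call that 6-25% of the planned 0.4. Neither input is in the article, the product applies only to an unadjusted completer mean, and the 0.4 was set for NPI-NH, not for the quality-of-life outcome.

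Nor is this a power problem: recruitment was planned on patients remaining after drop-out.

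**Conclusion.** The point holds, at modest size. The article fixes a primary population conditional on an event after randomisation. On its own drop-out figure this leaves out about 114-143 of 571 patients, deaths included. Any patients seen only at month 9 would come back in under the more generous reading.

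Analysing everyone protects against loss that differs by arm and is predicted by observed data. The benefit is zero with equal loss and selection, and of the order of 0.03 SD for a change contrast with a 10-point difference in loss. That figure rests on the assumed correlation of 0.6 and on loss driven by baseline; the article supports neither input. Bias from loss that depends on unobserved outcomes remains under either population. The change is worth making because it costs almost nothing and restores the comparison as randomised, not because a large bias has been shown.

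**What to change.** 1. Define the primary population as all consented patients of randomised units with a baseline score, analysed in their unit's arm.
2. Fit the planned repeated-measures mixed model to all available baseline, month 4 and month 9 data, with the baseline mean constrained equal between arms or with baseline adjusted for. State which.
3. Keep the month 4 completers as a sensitivity analysis, and word that set so that the place of month 9-only patients is clear.
4. Report deaths and other losses by arm and visit. Add one sensitivity analysis that handles death explicitly, for example by ranking it worst.

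The cost is wording in the analysis plan and one or two extra model runs, with no new data. The article says that the full analysis plan is still to be developed and that data collection is under way, so the change could still be pre-specified at that stage.
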